### Experimental hut trials to assess insecticidal durability

To further assess the entomological superiority of Interceptor^®^ G2 and Royal Guard^®^ over Interceptor^®^, experimental hut trials will be performed with field collected ITNs at 12-, 24- and 36-months post ITN distribution at the Cove experimental hut station against wild free-flying pyrethroid-resistant *An. gambiae *sensu lato (*s.l*.). The Cove experimental hut station is situated in a large rice-growing field within the study area of the cRCT. The vector population at Cove exhibits intense resistance to pyrethroids [32], but is susceptible to chlorfenapyr and pyriproxyfen [30]. To provide some comparison to pyrethroid-PBO nets, PermaNet^®^ 3.0 nets (a WHO prequalified deltamethrin plus PBO ITN by Vestergaard Sarl) that were distributed by the NMCP in the Didja district (7^°^20’N 1^°^56’E) of the Zou Department, a neighbouring community to the cRCT study area, at the same time as the cRCT will also be marked at baseline and withdrawn at each annual timepoint and assessed in the experimental hut trials alongside Interceptor^®^ G2 and Royal Guard®. Three sets of hut trials will be performed: one with 12 months old field nets, the second with 24 months old field nets and the third with 36 months old field nets. Fifty-four (54) field nets of each brand will be tested in the huts at each annual timepoint for a total of 54 nights with each field net spending only 1 night in the experimental huts. Comparison will be made with new unused nets of each type. Six replicates of unused nets of each ITN type will also be tested, and each net will be given six 4 × 4cm holes prior to the trial, following WHO procedures. The hut trials will consist of the following 9 treatments:Untreated net—6 replicatesInterceptor^®^ (new unused)—6 replicatesPermaNet^®^ 3.0 (new unused)—6 replicatesRoyal Guard^®^ Benin (new unused)—6 replicatesInterceptor^®^ G2 (new unused)—6 replicatesInterceptor^®^ field net (12/24/36-months)—54 replicatesPermaNet^®^ 3.0 field net (12/24/36-months)—54 replicatesRoyal Guard^®^ field net (12/24/36-months)—54 replicatesInterceptor^®^ G2 field net (12/24/36-months)—54 replicates

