### Experimental hut trials to compare 36 months old naturally aged field nets to washed nets

To investigate the capacity of ITN washing (20 times) to predict the performance of field aged ITNs, we will conduct another hut trial comparing nets of each ITN type washed 20 times to 36 months naturally aged field nets. ITN washing will follow WHO protocols for hut trials [13]. A total of 78 replicate 36 months old naturally aged field-collected nets of each ITN type will be tested over 78 nights. Six replicates of unwashed and washed nets of each ITN type will be tested, and each net will be given six 4 × 4cm holes following WHO guidelines. The hut trial will also be performed at the Côvè experimental hut station and will consist of the following 13 hut treatments.Untreated net—6 replicatesInterceptor^®^ (new unused)—6 replicatesPermaNet^®^ 3.0 (new unused)—6 replicatesRoyal Guard^®^ Benin (new unused)—6 replicatesInterceptor^®^ G2 (new unused)—6 replicatesInterceptor^®^ (washed 20 times)—6 replicatesPermaNet^®^ 3.0 (washed 20 times)—6 replicatesRoyal Guard^®^ Benin (washed 20 times)—6 replicatesInterceptor^®^ G2 (washed 20 times)—6 replicatesInterceptor^®^ (36-months field net)—78 replicatesPermaNet^®^ 3.0 (36-months field net)—78 replicatesRoyal Guard^®^ (36-months field net)—78 replicatesInterceptor^®^ G2 (36-months field net)—78 replicates

The trial will run for 13 weeks and will involve 13 consenting human volunteers sleeping in huts from dusk to dawn 6 days of each week of the trial. As with the other hut trials, treatments will be rotated each week using a randomized Latin Square Design and sleepers rotated daily and huts cleaned and aired on the 7th day of each week in preparation for the next rotation cycle. The trial will run for a total of 78 nights and the replicate 36 months old naturally aged field nets will be rotated between huts on successive nights (one net per night). Efficacy will be measured in terms of mosquito deterrence, mortality (72h), exiting, blood-feeding inhibition, reduction in fertility of blood-fed survivors as described earlier.

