### Sample size calculations

Sample size calculations are performed based on previous ITN durability data from Benin. For cohort 1, a sample size of 750 nets of each brand from 250 randomly selected households (assuming ~ 3 ITNs are distributed per household) in 5 study clusters was found sufficient to detect a 9.4% absolute difference (hazard ratio = 0.87) in ITN attrition rate assuming an attrition rate in the control arm of 70% over the 3 years and an intra-cluster correlation coefficient of 0.03. For cohort 2, a total of 522 ITNs will need to be withdrawn over three years and assuming a loss rate of 70% a total of 1800 ITNs will be marked per study arm at baseline. To reduce the impact of the durability study on the outcomes of the cRCT, cohort 2 nets will be obtained from households in the buffer areas of the selected clusters to exclude the core areas used for the cRCT sampling.

For each experimental hut trial and at each timepoint, data on the number of mosquitoes per night and the magnitude of the different random effects (huts, sleepers, nights and observational error) will be reviewed after the first round of 9 or 13 weeks and power calculations conducted by simulation using previously described methods [33]. Power analysis will determine whether the hut trial has a desired 80% power to detect superiority in mosquito killing of any new unused dual AI ITN over the new unused pyrethroid-only net, assuming a true underlying extra mortality from the dual AI net of 40%. A second round of hut trial would be performed if the desired level of power is not achieved.

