### Statistical analysis

Data from the surveys at 6, 12, 24, and 36 months will be used to calculate attrition, functional survival and median survival time using Kaplan–Meier estimators. For functional survival, nets reported as given away, sold, or stolen will be excluded from the analysis. Negative binomial regression will be used to compare hole surface area between the different ITN types. Data on WHO cone bioassays and tunnel tests will be obtained from 30 nets of each product type sampled at each time point. A chi-squared test will be used to assess the proportion of nets of each ITN type passing the WHO criteria for alphacypermethrin, chlorfenapyr and pyriproxyfen bioefficacy based on combined cone and tunnel tests. Proportional outcomes (mortality, blood-feeding, exophily) from the experimental hut trials will be compared at each time point using mixed effects logistic regression, with huts, sleepers, net replicate and nightly observational error included as random or fixed effects [33]. Numerical outcomes (hut entry) will be compared using negative binomial regression. A separate model will be fitted for each outcome to determine whether there is (i) a significant change over time, and (ii) a significant difference between ITNs washed 20 times and 36-month-old naturally aged ITNs. Analysis will be performed on STATA or the package *lme4* of the R software.

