In standard ITN experimental hut evaluations, the performance of nets washed 20 times is widely accepted as a measure of their efficacy after 3 years of field use and ITN products have been prequalified by WHO based on their performance after 20 washes. However, not much is known about how this washing process and number of washes relates to the natural ageing of nets in households. The hut trial comparing naturally aged nets to washed nets in our study provides an opportunity to investigate this claim. To further support this objective, the number of times householders’ wash their nets over 3 years of household use and the washing methods used will also be investigated. Another key objective of this study is to use mathematical models to determine whether the entomological performance of ITNs in the experimental hut trials performed in this study could be predictive of their performance in the cRCT. The findings from this modelling study will provide further insights into the role of experimental hut trials in the dual ITN product development process.

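### The hut-trial analysis tests for a difference where the question is whether 20 washes predict field ageing, and it names no reference for change over time

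*Protocol article*

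**What the plan says.** **Washed versus aged.** The Protocol article's section on the hut trial of washed and 36-month nets gives the purpose as "To investigate the capacity of ITN washing (20 times) to predict the performance of field aged ITNs". The last paragraph of the Background says the same. The Discussion notes that performance after 20 washes is accepted as a measure of efficacy after three years and that products have been prequalified on it. It says that this trial "provides an opportunity to investigate this claim". The trial runs 78 nights with 78 field nets and six washed nets of each type.

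The Statistical analysis section models each outcome separately, and its criterion for this comparison is "a significant difference between ITNs washed 20 times and 36-month-old naturally aged ITNs". It gives no margin and does not say how a non-significant result will be interpreted.

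The only hut power criterion, under Sample size calculations, is "desired 80% power to detect superiority in mosquito killing of any new unused dual AI ITN over the new unused pyrethroid-only net". The extra mortality assumed there is 40%. That check also decides whether a second round is run.

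**Change over time.** The section on hut trials for insecticidal durability says "Three sets of hut trials will be performed: one with 12 months old field nets, the second with 24 months old field nets". The last of the three uses 36-month nets. For ageing, the Statistical analysis section looks for "a significant change over time" and does not say against which reference. New unused nets of each type and an untreated net run in every trial. Reductions in entry, blood-feeding and fertility are defined relative to the untreated control; mortality and exiting are not. The susceptibility of the wild population is tested during each trial.

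**The concern.** Whether washing predicts ageing is a question of agreement. A test of no difference cannot establish agreement. With sparse data a real gap passes unnoticed, and with plentiful data a trivial gap becomes significant. At stake is a proxy that the article itself says is used in prequalification. The trial could also pass its own power check and still say little about washed against aged nets.

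The time test raises a separate problem. For field nets, age and trial occasion move together: 12-month nets meet only the mosquitoes of the first trial, and 36-month nets only those of the third. If the wild population changes between trials, a raw comparison of field nets shows that change as if the nets had lost activity. Mortality and exiting are the most exposed, because their definitions include no concurrent control.

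**Working it through.** **The plan's own figure.** The 80% is a target to be checked by simulation after the first round. Control mortality, catch size and variance components are not given, so it cannot be reproduced. For scale, take six new nets per arm, 54 nights, 10% to 40% mortality on the pyrethroid-only net, 3 to 20 mosquitoes per night, and night and between-net SDs (logit) from 0.5 and 0.2 up to 1.0 and 0.5. Read as 40 percentage points, the extra mortality gives power of 98% to 100%. Read as a 40% relative increase, it gives 12% to 96%. The article does not say which is meant. On the absolute reading the check is passed easily, and on either reading it does not concern washed against aged nets.

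**Washed versus 36-month nets**

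Inputs from the document: 78 nights (13 weeks × 6), 6 washed nets and 78 field nets per type. Assumed: m = 10 mosquitoes per net-night, mortality p = 0.5, night-level SD s = 0.5 to 1.0 (logit), between-net SD t = 0 or 0.5, the same for washed and field nets, two-sided 5% test.

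Variance of the log odds ratio = 2 × [1/(78 × m × p(1 − p)) + s²/78] + t²/6 + t²/78

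The first term in brackets is 1/(78 × 10 × 0.25) = 0.00513.

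- s = 0.5, t = 0: 2 × (0.00513 + 0.00321) = 0.0167, SE 0.129
- s = 1.0, t = 0: 2 × (0.00513 + 0.01282) = 0.0359, SE 0.189
- With t = 0.5, add 0.25/6 + 0.25/78 = 0.0449: SE 0.248 and 0.284

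A true fall from 50% to 40% is a log odds ratio of ln(0.4/0.6) = −0.405. A fall to 45% is ln(0.45/0.55) = −0.201. Power is approximately Φ(|log OR|/SE − 1.96).

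| s | t | SE | Power, 10 points | Power, 5 points | 95% CI if the observed OR is 1 |
|---|---|---|---|---|---|
| 0.5 | 0 | 0.129 | 88% | 34% | 0.78 to 1.29 |
| 1.0 | 0 | 0.189 | 57% | 18% | 0.69 to 1.45 |
| 0.5 | 0.5 | 0.248 | 37% | 13% | 0.62 to 1.63 |
| 1.0 | 0.5 | 0.284 | 30% | 11% | 0.57 to 1.74 |

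Over a wider grid (3 to 20 mosquitoes per night, t = 0.2 to 0.5), a true 10-point gap is non-significant 16% to 76% of the time.

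**Can agreement be shown?** For illustration only, take a margin of 0.70 to 1/0.70, so |ln 0.70| = 0.357. At t = 0.5 the six washed nets alone contribute an SE of √(0.25/6) = 0.204, and 1.96 × 0.204 = 0.400. A 95% CI then cannot fit inside that margin, however many mosquitoes are caught. Over the wider grid, with the two nets truly equal, the chance of showing agreement is 0% to 48% with a 95% CI and 0% to 66% with a 90% CI.

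**Change over time**

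Assume mortality on an unchanged net falls from 30% in one trial to 20% in a later one. The odds ratio is (0.2/0.8)/(0.3/0.7) = 0.58, with no ageing at all. With 54 net-nights, 10 mosquitoes and SD 0.8, the variance is (1/2.1 + 0.64)/54 + (1/1.6 + 0.64)/54 = 0.0441, so SE = 0.210. Then z = 0.539/0.210 = 2.57, and a raw comparison is significant about 73% of the time. If the new net of the same product shifts equally on the logit scale, the field-versus-new contrast is unchanged.

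**The case against.** The strongest reply on washing is that the article never says non-significance will be taken as agreement. The listed objective is only to compare, the planned mixed logistic model yields odds ratios and intervals anyway, and the modelling section separately asks whether washed-net or aged-net inputs better capture prevalence in the parent trial. All of that stands. A reader might infer that the investigators have adopted a rule equating non-significance with agreement; the text does not support that. What remains is that the article states a criterion for this hut comparison, the criterion is a difference test, and neither the objective nor the modelling supplies another.

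On ageing, a reader might infer that the new nets are excluded from the time test or that the design is confounded. Neither follows. Silence about the reference is not exclusion, the article plans comparison with new nets in every trial, and vector susceptibility is monitored. A reader might also infer that the conclusion on insecticide loss rests on the huts alone. It does not: chemical content, and laboratory bioassays on maintained strains beside new nets, also bear on it. Model detail may sit in an analysis plan that is not shown. The point is therefore limited to the unnamed reference, and matters most for mortality and exiting.

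**Conclusion.** The concern holds in limited form. A difference test without a margin cannot support the claim that washing predicts field ageing, and the stated power check does not protect this contrast. The power range of 57% to 88% for a 10-point gap is the favourable case, with no variation between nets; a between-net SD of 0.5 brings it to about 30% to 37%. Catch size, mortality and both SDs are assumptions; only the nights and net counts come from the document. If washed nets vary less than assumed, power lies nearer the upper range.

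For change over time, the weakness lies in how the test is stated. The odds ratio of 0.58 shows what an assumed shift between trials would do to a raw comparison. It is not evidence that such a shift occurred.

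**What to change.** 1. **Washed versus aged.** For each net type, report the washed-versus-36-month odds ratio with its 95% CI, with net as a random effect. Set a justified margin before the 36-month hut data are analysed. Conclude *agrees* if the interval lies inside the margin, *differs* if it lies wholly outside, and *inconclusive* otherwise. The margin is for the investigators to justify; 0.70 above is only an illustration.
2. **Ageing.** Define it as the field-versus-new contrast of the same product within each trial. Fit one model across the 12-, 24- and 36-month trials with a trial effect, and test the treatment-by-trial interaction.

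Both are changes of analysis wording and need no new data, since new nets are already in every trial. The article's status section reports hut work on nets up to 24 months as ongoing, so at publication a margin could still be set in time. The cost is that, with six washed nets per type, *inconclusive* may be a common answer. If between-net variation is large, a firm statement of agreement may need more washed nets; more nights with the same six would not be enough.

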### Ethical considerations

Ethical approval for this study has been obtained from the ethics review boards of the Ministry of Health in Benin (N°6/30/MS/DC/DRFMT/CNERS/SA), the institutional review board of the London School of Hygiene and Tropical Medicine (N°16,237), and the WHO Research Ethics Review Committee (ERC.0003153). The cRCT is registered on clinicaltrials.gov (NCT03931473).

Heads of households involved in the durability study will give informed consent prior to their participation in the study. The consent form will be written in French and explained to them in their local language. Where the individual is unable to read or write, their fingerprint will be taken, and a signature obtained from a witness to the informed consent procedure. All personal data will be anonymized prior to data processing. Written informed consent will also be obtained from all human volunteer sleepers for experimental hut trials prior to participation. Sleepers will be offered a free course of chemoprophylaxis spanning the duration of the study and 4 weeks following its completion to mitigate malaria infection risk. Approval for use of guinea pigs for tunnel tests has been obtained from the LSHTM Animal Welfare Ethics Review Board (Ref: 2020–01). Guinea pig colonies will be maintained according to institutional standard operating procedures (SOPs) developed in line with relevant national regulation and UK Research and Innovation policies for the use of animals for scientific research purposes.

## Discussion

This paper describes the methodology for evaluating the physical and insecticidal durability of two dual AI ITNs (Interceptor^®^ G2 and Royal Guard^®^) as part of an ongoing cRCT in Benin. Both nets are being compared to a WHO prequalified alpha-cypermethrin net (Interceptor^®^). By investigating the attrition and fabric integrity of the study nets, we will generate data needed for planning their replacement and for making programmatic and procurement decisions [14] once they are deployed more widely. Previous studies have shown that householders distinguish between ITN products and tend to overwhelmingly prefer polyester ITNs over polyethylene ITNs [34]. By investigating householders’ preferences and perceptions of the different ITN fabric types used in the formulation of the study nets (polyethylene for Royal Guard^®^ and polyester for Interceptor^®^ G2 and Interceptor^®^), we will also provide more insights into how fabric type may affect ITN retention and overall impact in Benin.

Dual AI ITNs cost significantly more than standard pyrethroid nets due to the additional non-pyrethroid active ingredient on these nets. To ensure value for money, it is essential to closely monitor the insecticidal activity of the non-pyrethroid component in these nets using insecticide durability bioassays. Current WHO ITN insecticide durability guidelines were developed mostly for pyrethroid-only nets hence the methods and recommended strains were suited to their rapid mode of action [13]. We propose subtle modifications to these standard laboratory bioassay methods and to recently developed consensus SOPs [35] to facilitate monitoring of the insecticidal durability of chlorfenapyr in Interceptor^®^ G2 and pyriproxyfen in Royal Guard® while improving the efficiency of the bioassays. First, the mosquito strains used in laboratory bioassays with dual AI ITNs must allow assessment of the non-pyrethroid insecticide in the net without interference from the pyrethroid component. For assessment of pyriproxyfen in Royal Guard® for example, it is essential that enough blood-fed survivors are obtained post ITN exposure. By using a high intensity pyrethroid-resistant strain (*An. coluzzii* Akron) we will substantially reduce the toxicity and confounding effect of the pyrethroid allowing a more realistic assessment of the non-pyrethroid components.

For Interceptor^®^ G2 bioassays, we will perform only tunnel tests with the pyrethroid resistant Akron strain focusing primarily on evaluating the activity of the chlorfenapyr component of the net. Chlorfenapyr acts on the respiratory system of mosquito vectors hence its activity against malaria mosquitoes is optimal when they are active and host-seeking at night in line with their nocturnal behaviour [19]. The tunnel test being an overnight bioassay that allows free mosquito movement therefore constitutes a more appropriate test method for evaluating the efficacy of chlorfenapyr in Interceptor^®^ G2 compared to daytime 3 min cone bioassays. In addition, because the alpha-cypermethrin component in Interceptor^®^ G2 is relatively low (~ 50% of what is typically applied on ITNs) its insecticidal activity would likely be more limited and less durable even in cone bioassays. The chlorfenapyr component is therefore expected to maintain the killing effect of these nets as they age. By testing Interceptor^®^ G2 nets only in tunnels we will ensure high efficiency of the laboratory bioassays.

For Royal Guard^®^, the insecticidal durability of the alpha-cypermethrin component will be investigated following current WHO ITN guidelines while modified bioassay methods will be used to assess the activity of pyriproxyfen. Pyriproxyfen acts by sterilizing adult mosquitoes and based on this mode of action, two different methods have been proposed for investigating its impact on ITNs; assessment of oviposition inhibition and dissection of mosquito ovaries to determine their developmental stage [20, 22, 35, 36]. The oviposition inhibition method directly measures the impact of pyriproxyfen on mosquito offspring by holding exposed blood-fed mosquitoes in oviposition chambers to give them opportunity to lay eggs and determining the proportional reduction in numbers laying relative to unexposed mosquitoes. The dissection method is based on the physiological impact of pyriproxyfen on the ovarian development of adult female mosquitoes leaving them visibly damaged and halting their follicular maturation process [37]. With this method, mosquito ovaries are dissected, and their developmental stage assessed to determine whether they are fertile or not; mosquitoes with stage V fully developed ovaries are considered fertile. While both methods have been effectively used to measure the impact of pyriproxyfen on nets [20, 36], preliminary studies comparing them demonstrated that the dissection method was more reproducible, more sensitive and less time consuming (unpublished data). Hence, given the volume of bioassays envisaged in this study, the mosquito ovary dissection method will provide a higher throughput alternative for assessing the sterilizing effect of pyriproxyfen in Royal Guard®. In addition to its sterilizing effects, pyriproxyfen has also been demonstrated to shorten the lifespan of adult mosquitoes when applied on ITNs [38]. However, the evaluation of this life shortening effect in laboratory bioassays requires that mosquitoes are observed for several weeks post-exposure which would be very time consuming and too demanding to be performed in routine ITN insecticidal durability studies.

Current WHO ITN evaluation guidelines define specific thresholds for determining the efficacy of ITNs in insecticidal durability bioassays. Nets that induce ≥ 95% knockdown and/or ≥ 80% mortality in cone bioassays or ≥ 80% mortality and/or ≥ 90% blood feeding inhibition in tunnel tests are considered efficacious. While proposing these same efficacy criteria for the laboratory bioassays for alpha-cypermethrin and chlorfenapyr bioefficacy in the study nets, it is recognized that these cut-offs were primarily developed for fast-acting pyrethroid insecticides on nets and may need to be modified for non-pyrethroid insecticides. Indeed, new draft WHO guidelines proposed for ITN prequalification aim more for a weight of evidence approach and do not allude to specific efficacy thresholds [39]. The weight of evidence approach may be suitable for assessing individual ITN products but could be challenging for comparing between ITN product brands and making programmatic and procurement decisions, which is usually the main objective for ITN durability studies. Efficacy criteria for the sterilizing effects of pyriproxyfen on ITNs are yet to be defined in WHO guidelines. Further studies investigating correlations between the sterilizing effects of Royal Guard^®^ nets in laboratory bioassays and their epidemiological performance against clinical malaria in the current trial, may contribute towards the identification of a suitable cut-off for the impact of pyriproxyfen in ITN durability studies.

Despite the methodological modifications we propose for laboratory bioassays in this study, it is unclear whether typical ITN laboratory bioassay techniques (cone bioassays and tunnel tests) would be sufficiently informative of the insecticidal durability of dual AI ITNs as these methods were developed for pyrethroid-only ITNs [22, 23]. Other bioassay methods under consideration for dual AI ITNs are the WHO wire ball assay [13, 40] and the net-in-tube test [22] that provide a more forced contact between the mosquito and the net potentially resulting in greater levels of AI pick up from the net than in cone bioassays. Given the mode of action of chlorfenapyr described earlier, these assays would be less suitable for the assessment of its activity in Interceptor^®^ G2 as they provide less opportunity for mosquito movement and host seeking. In addition, our preliminary studies assessing the baseline activity of pyriproxyfen in Royal Guard^®^ using the net-in-tube method resulted in higher levels of mosquito mortality with high intensity pyrethroid-resistant strains leaving very few blood-fed survivors for ovarian dissection. These methods due to the forced contact they provide may therefore be less suitable for monitoring changes in the bioefficacy of the pyriproxyfen component in Royal Guard^®^ over time. Experimental hut trials are more representative of real-life settings and are widely used for evaluating ITNs under semi-field conditions for product development and for decision-making about their deployment [41]. In these trials, ITNs are tested overnight against wild free-flying vector mosquitoes entering naturally into the huts in the presence of a human volunteer and the levels of blood-feeding inhibition and mortality rates achieved are used as proxies for their capacity to provide personal and community protection to users. Hence the assessment of field collected ITNs in experimental hut trials proposed in this study will provide additional insights into the impact of these dual AI ITNs against malaria as they age under operational conditions.

In standard ITN experimental hut evaluations, the performance of nets washed 20 times is widely accepted as a measure of their efficacy after 3 years of field use and ITN products have been prequalified by WHO based on their performance after 20 washes. However, not much is known about how this washing process and number of washes relates to the natural ageing of nets in households. The hut trial comparing naturally aged nets to washed nets in our study provides an opportunity to investigate this claim. To further support this objective, the number of times householders’ wash their nets over 3 years of household use and the washing methods used will also be investigated. Another key objective of this study is to use mathematical models to determine whether the entomological performance of ITNs in the experimental hut trials performed in this study could be predictive of their performance in the cRCT. The findings from this modelling study will provide further insights into the role of experimental hut trials in the dual ITN product development process.

